### Interventions

2.5

#### Development of the intervention program

2.5.1

A research team (a total of five members) comprising one professor of nursing, one associate professor of nursing, two doctoral students, and one master’s student will be established to develop the initial framework of the intervention program. Guided by the ICOPE model, the study will focus on the management and care pathways for the decline in intrinsic capacity, incorporating findings from previous studies and guideline recommendations. The intervention program, designed for the long-term care of old patients with disabilities in nursing homes, will adopt a multi-dimensional approach to address the decline in intrinsic capacity. It will encompass motor function, cognitive ability, vitality, sensory perception (vision and hearing), psychological function, and health education to enhance the overall health and quality of life of old patients with disabilities.To ensure the scientific validity and feasibility of the intervention program, this study will adopt the Modified Delphi Method to refine and finalize the proposal (30, 31). The specific steps are as follows: (1) A research team will be established. (2) Based on prior research and in-depth discussions, the team will develop an expert consultation questionnaire comprising three key components: ① A situation description module, which will outline the purpose of the consultation, the research background, and the theoretical framework; ② An importance assessment module, where experts will evaluate the significance of various elements of the intervention program; ③ An expert authority assessment module, which will gather information on each expert’s background, professional experience, and familiarity with the research topic. (3) The research team will select 15–50 experts from relevant fields to ensure the authority and representativeness of the consultation process (32). (4) The first round of expert consultation will be conducted, with responses undergoing preliminary analysis and the questionnaire revised accordingly based on expert feedback. (5) A second round of expert consultation will then be carried out. If the level of consensus among experts does not meet the predefined threshold, additional rounds will be conducted as needed. If sufficient consensus is reached, the consultation process will be concluded. Statistical analysis will be performed on the final consultation results, and the intervention program will be revised accordingly based on expert feedback. Once a stable consensus is reached, the research team will finalize the intervention program (Table 1), ensuring its scientific rigor, feasibility, and clinical applicability.

**Table 1 tab1:** ICOPE-based long-term care intervention program for old patients with disabilities in nursing homes.

Main domain	Intervention indicators	Intervention content	
1. Motor function	1.1 Aerobic exercise	1.1.1 Walking [figure not shown]	(1) Walk facing forward: Keep your gaze straight ahead and avoid looking down at the ground. When stepping forward, first firmly place your heel on the ground, followed by the toes. Keep your shoulders relaxed and allow your arms to swing naturally to help maintain balance, ensuring a stable and safe walking posture. (2) Each walking session consists of 5 sets, with each set lasting 2–5 min. After completing one set, take a 1-min rest between sets to adjust your posture and relieve physical fatigue before proceeding to the next set. This cycle continues until all 5 sets are completed.
	1.2 Resistance training	1.2.1 Lifting a water bottle [figure not shown]	(1) Seated Position and Movement: While performing the exercise in a seated position, ensure that both hands hang naturally at your sides, each firmly holding a water bottle. Slowly bend your elbows toward your chest while engaging your arm muscles, lifting the bottles smoothly until they reach shoulder height. Hold this position briefly to feel the contraction and extension of the arm muscles. (2) Repetitions and Rest: Each training session consists of 3 sets of 12 repetitions. After completing one set, take a 1-min rest before proceeding to the next set. • Progressive Intensity: After six weeks of continuous training, to further enhance the effectiveness of the exercise, the amount of water in the bottles can be gradually increased to intensify the workout. It is essential to increase the water level progressively, avoiding excessive increments at once to ensure a safe and steady progression in training.
		1.2.2 Squeezing a ball [figure not shown]	(1) Hand Exercise Technique: During the exercise, gradually apply pressure to squeeze the ball at a slow and controlled pace, feeling the tension and contraction in the hand muscles. Once reaching maximum grip strength, hold the position briefly. Then, slowly release the grip, allowing the hand muscles to relax and stretch. Repeat the squeezing and releasing motion to complete one set. (2) Repetitions and Rest: Each session consists of 3 sets of 12 repetitions (squeeze and release). After completing one set, take a 1-min rest before proceeding to the next. Once all 3 sets are completed with one hand, switch to the other hand and repeat the exercise following the same steps to ensure balanced hand muscle strengthening.
	1.3 Balance training	1.3.1 Simulated sitting motion [figure not shown]	(1) Exercise Technique: Stand in front of a table and position yourself securely. Slowly bend your knees and lower your hips as if you are about to sit down, maintaining a smooth and controlled motion throughout. Once you reach the desired squat depth, gradually engage your muscles to return to the initial standing position. To ensure safety during the exercise, it is recommended to place a chair behind you for support if needed. (2) Repetitions and Rest: Each session consists of 3 sets of 12 repetitions. After completing one set, take a 1-min rest before proceeding to the next set.
		1.3.2 Walking on tip toes and heels [figure not shown]	(1) Exercise Technique: Stand up steadily and hold onto the edge of a table or a nearby handrail for support. Shift your body weight onto your toes, using them as the primary support, and take seven controlled steps forward while maintaining balance. After completing the toe-walking sequence, take a brief rest to adjust. Then, shift your weight onto your heels, using them as the main support, and walk at least seven steps forward. This exercise effectively strengthens leg muscles and improves balance. (2) Repetitions and Rest: Each session consists of 3 sets of 12 repetitions. After completing one set, take a 1-min rest before proceeding to the next.
	1.4 Flexibility training	1.4.1 Seated arm stretch [figure not shown]	(1) Exercise Technique: Sit securely on a chair, ensuring a slight gap between your back and the chair’s backrest. Let your arms hang naturally at your sides, then slowly extend them backward, attempting to grasp the back of the chair. Once you successfully hold the chair, maintain this position while pushing your chest forward until you feel a slight stretch in your arm muscles. Hold this posture for 10 s, then relax for 5 s while keeping your hands on the chair. (2) Repetitions and Rest: Each session consists of 3 sets of 3 repetitions. After completing one set, take a 30-s rest before proceeding to the next set.
		1.4.2 Overhead arm stretch [figure not shown]	(1) Exercise Technique: This exercise can be performed in either a standing or seated position. Once ready, interlock your fingers and extend your arms straight upward, as if reaching for the ceiling. Hold this stretch for 10 to 12 s, fully feeling the extension in your arm muscles. After each repetition, take a brief pause and relax your arms for 5 s to allow the muscles to recover before repeating the movement as needed. (2) Repetitions and Rest: Each session consists of 3 sets of 3 repetitions. After completing one set, take a 30-s rest before proceeding to the next set.
2. Vitality	2.1 Balanced diet	2.1.1 Dietary recommendations	(1) Adjusting Meal Plans: Based on the nutritional status of disabled older adults, nutritionists are advised to modify dietary plans accordingly to meet their specific needs. (2) Establishing Healthy Eating Habits: Older adults often have insufficient food intake. To encourage greater food consumption, it is recommended that they dine in groups, fostering a more enjoyable and social eating experience.
		2.1.2 Oral nutritional Supplementation	(1) Oral Nutritional Supplementation: Additional high-quality protein, energy (carbohydrates), and essential micronutrients (such as vitamins and minerals) can be provided based on individual needs, preferences, and physical conditions. (2) Protein Supplementation: As protein absorption declines with age, it is recommended that older adults increase their protein intake to maintain muscle strength and overall health.
	2.2 Multimodal exercise	Refer to 1. Motor function	
	2.3 Weight management	Regular weight monitoring	Closely monitor body weight once per week.
3. Psychological function	3.1 Psychological interventions	3.1.1 Cognitive behavioral therapy	(1) Identifying problems in daily life. (2) Becoming aware of thoughts, emotions, and beliefs related to these problems. (3) Recognizing negative or inaccurate thoughts. (4) Restructuring these thoughts to make them more realistic.
		3.1.2 Problem-solving counseling	For disabled older adults experiencing depressive symptoms or some degree of social dysfunction (without a diagnosed depressive episode or disorder), biweekly counseling sessions will be conducted. These sessions aim to identify psychological issues in a timely manner and provide support and guidance as needed.
		3.1.3 Behavioral activation	Behavioral activation involves encouraging disabled older adults to participate in rewarding activities to help alleviate depressive symptoms.
		3.1.4 Life Review Therapy	Digital reminiscence intervention system, through the mobile (mobile phone/tablet) clicking on the module as well as voice interaction, to complete the construction of reminiscence themes and reminiscence resource library and other digital reminiscence content based on subthreshold depressed older adults. In total, it includes a number of modules such as personal information, assessment module, age footprint, chronological impression, point reward, and settings.
	3.2 Multimodal exercise	Refer to 1. Motor function	
	3.3 Mindfulness practice	3.3.1 Mindful movement	There are various types of mindfulness practices, with one of the most commonly used methods being sitting or lying quietly while focusing attention on the sensation of breathing. Additionally, mindful movement, such as practicing mindfulness while walking, can be beneficial for some individuals.
4. Cognitive ability	4.1 Cognitive stimulation	4.1.1 Computer-assisted cognitive system	With the help of mouse and keyboard operation, the computerized cognitive aid system (virtual supermarket training system) can complete the preset task modules of the system in order to experience virtual shopping in an immersive way, and then achieve the goal of cognitive training in multiple fields. The system covers nine task modules, each corresponding to a precise cognitive training, specifically: ‘Memory list’ to train intentional memory; ‘Map navigation’ to exercise the ability to navigate; ‘Voice broadcasting Each module precisely corresponds to a cognitive training task, as follows: ‘Memory list’ to train intentional memory; ‘Map navigation’ to improve navigation skills; ‘Voice announcement’ to enhance unintentional memory; ‘Labeling’ to strengthen verbal naming; ‘Voice cashier prompts’ to enhance verbal receptivity; ‘Payment calculation’ to train ‘Payment Calculator’ trains numeracy; “Date Code” fosters orientation; “Prize Redemption” exercises sustained attention; and “Bus Decision Making” enhances decision-making skills. By participating in these tasks, users can train their cognitive abilities in multiple domains, such as memory, language function, executive function, attention and time orientation.
	4.2 Multi-modal exercise	Refer to 1. Motor function	
5. Sensory	5.1 Hearing devices	5.1.1 Hearing aids	Hearing aids are often the most effective solution for age-related hearing loss. They amplify sound and are beneficial for most individuals. Hearing aids can be worn over or inside the ear, making them convenient to use. However, it is essential to explain to older adults that hearing aids do not cure or reverse hearing loss, but rather help improve auditory perception.
		5.1.2 Cochlear Implants	Cochlear implants are surgically placed inside the ear to convert sound into electrical impulses, which are then transmitted to the auditory nerve. A thorough evaluation is necessary to determine whether a cochlear implant is suitable. If implantation is not possible or appropriate, older adults and their families should be provided with information and training on lip reading and sign language as alternative communication methods.
		5.1.3 Audio induction loops and personal sound amplifiers	Audio induction loops and personal sound amplifiers are also effective. An audio induction loop (or hearing loop) consists of one or more wires placed around a designated space, such as a conference room or service counter. These wires transmit sound signals from a microphone and amplifier directly to compatible hearing aids, improving auditory clarity in specific environments.
		5.1.4 Social and natural environment	(1) Regular social interaction can help reduce the risk of cognitive decline, depression, and other emotional and behavioral consequences of hearing loss. (2) Social support networks can provide assistance during particularly challenging situations. (3) Peers and caregivers play a crucial role in preventing loneliness and social isolation. They may need guidance on how to facilitate social engagement, such as maintaining communication with individuals with hearing loss and organizing activities that encourage their participation in social networks.
	5.2 Communication strategies for caregivers		(1) Ensure your face is visible when speaking to the individual. (2) Maintain adequate lighting on your face to help the listener see your lips clearly. (3) Gain the attention of the person with hearing loss before speaking. (4) Minimize distractions, particularly loud noises and background sounds. (5) Speak clearly and at a moderate pace—do not shout. (6) Do not avoid communicating with individuals with hearing loss, as social isolation can lead to depression and emotional distress.
	5.3 Vision rehabilitation	5.3.1 Magnifiers	Magnifiers can often provide assistance for individuals with vision impairment. Simple magnifiers are affordable and come in various magnification levels. However, they only enlarge nearby objects. If a basic magnifier does not adequately address the issue, a comprehensive eye examination is recommended.
		5.3.2 Irreversible vision loss	Many individuals experience low vision that cannot be fully corrected with prescription glasses. For these individuals, assistive visual devices such as desktop or portable magnifiers offer higher magnification than regular eyeglasses. These devices can enhance near-vision tasks, including reading books or newspapers, identifying currency, reading labels, and examining small objects or specific parts of larger objects.
	5.4 Adapting to low vision	5.4.1 Improving lighting	Good lighting is especially important for near vision. Ideally, light should come from the side to prevent shadows from interfering with visibility.
		5.4.2 Reducing glare	Bright lighting is generally beneficial; however, sunlight or intense artificial light may cause discomfort for some individuals. Adjusting brightness or using diffused lighting can help reduce glare.
		5.4.3 Removing obstacles	Hazards such as furniture and other hard objects should be removed from the daily paths of individuals with low vision. If removal is not possible, these objects should always remain in a fixed location to prevent accidents.
		5.4.4 Enhancing contrast	Good contrast between and within objects makes them easier to see, locate, or avoid. Examples include high-contrast markings on stair edges (especially for individuals with vision in only one eye), using colored plates to make food more visible, and writing with black pens for better readability. Individuals with low vision, their family members, and caregivers can enhance the visibility and safety of household and kitchen tools by adding color-coded handles. For instance, wrapping brightly colored tape around knife handles or painting them can help improve clarity and safety.
6. Health education and guidance	6.1 Prevention guidance for disability and related diseases	Thematic education sessions will be held once per week, covering a range of topics including disability care management, long-term care management, exercise guidance, cognitive decline management, social interaction guidance, psychological well-being support, balanced diet recommendations, sleep guidance, proper medication use, fall prevention, assistive device usage, and disease prevention and treatment education.	
6.2 Medication guidance			
6.3 Sleep and rest			
6.4 Use of assistive devices			

#### Pre-experiment

2.5.2

A one-week pilot study will be conducted using the preliminary intervention program with 10 older adults with mild to moderate disabilities in a nursing home in Changchun to assess their feedback and refine the design and implementation strategy of the intervention plan. The results are expected to indicate that, during the initial phase of the intervention, participants will generally be unfamiliar with the intervention measures and may exhibit a certain level of apprehension, highlighting the need for a gradual process of familiarization and adjustment. Additionally, nursing home staff are likely to report that they have not previously been exposed to a systematic long-term care intervention program, thereby underscoring the necessity for targeted training on intervention procedures and key implementation considerations.Based on these findings, the research team will revise the intervention program accordingly. Modifications will include strengthening pre-intervention training sessions for nursing home staff to facilitate smooth and consistent implementation. During the intervention period, staff will be encouraged to offer individualized assistance tailored to the needs of each older adult, with a gradual shift toward independent participation as participants become more comfortable with the content, ensuring both safety and active engagement. Regarding the psychological well-being component, in light of staff feedback, the originally planned weekly problem-solving consultation or therapy sessions will be adjusted to a biweekly schedule. Similarly, the frequency of the reward system will be modified from once per week to once every 2 weeks, in order to balance participant engagement with the practical feasibility of program delivery.

#### Formal intervention

2.5.3

##### Intervention group

2.5.3.1

Before the intervention, two preparatory practice sessions will be conducted over a 2-week period. During the first week, a trained researcher will introduce and demonstrate the equipment operation procedures, guiding participants through the exercises to help them become familiar with the system’s functions and usage methods. In the second week, two researchers will evaluate each participant’s operational proficiency and provide individualized instruction as needed, ensuring that all participants develop a clear and accurate understanding of how to use the system independently. In addition, at the conclusion of the training, participants will be given a video tutorial recorded by the research team, demonstrating the operation procedures and key methods. This resource will support those who may require additional time and reinforcement to gain confidence with the system.

The intervention group will participate in the study for a total duration of 16 weeks, comprising a 12-week intervention phase followed by a 4-week follow-up phase. The old patients with disabilities in intervention group will take part in the “ICOPE-Based Long-Term Care Intervention Program for old patients with disabilities in Nursing Homes” (Table 1), in addition to receiving the same routine care as the control group. The intervention program was designed to enhance physical, nutritional, psychological, cognitive, and sensory functions, as well as to provide comprehensive health education and guidance. It comprised the following six components: (1) Motor function: training incorporated resistance training, aerobic exercise, flexibility training, and balance training, with each session lasting 30–45 min, twice per week. (2) Nutrition: nutritional support was tailored to individual needs based on nutritional status assessments, ensuring a balanced diet and appropriate oral supplementation. (3) Psychological function: ① Problem-solving counseling or therapy, 30–45 min per session, once every 2 weeks; ② Behavioral activation with a reward system, 30–45 min per session, once every 2 weeks. (4) Cognitive function: computer-assisted cognitive training using the virtual supermarket training system, 30–45 min per session, twice per week. (5) Sensory function: ① Auditory training using cards, 30–45 min per session, once weekly; ② Visual training using a bouncy ball, 30–45 min per session, once weekly. (6) Health education and guidance: it was delivered through thematic education sessions, covering essential health topics, conducted once per week for 30–45 min. All intervention sessions will be conducted in the nursing home’s activity room to ensure accessibility and consistency for participants.

##### Control group

2.5.3.2

The old patients with disabilities assigned to the control group will continue their routine daily activities and receive standard care provided by the nursing home, without exposure to any components of the intervention program. During the intervention period, researchers will conduct non-intrusive observation and data collection, refraining from making any active changes to participants’ dietary patterns, daily routines, or recreational activities.

### Outcome measures

2.6

#### Quantitative outcome measures

2.6.1

The participants in both the intervention and control groups will be assessed on their intrinsic capacity, covering six domains, including cognitive function, motor function, vitality, vision, hearing, and depression. Assessments will be conducted at T_0_, T_1_, and T_2_. For a detailed description of data collection, refer to Table 2.

**Table 2 tab2:** Overview of data collection.

Measures	T_0_	T_1_	T_2_
Demographics	△		
ICOPE screening tool	△	△	△
MMSE	△	△	△
SPPB	△	△	△
MNA	△	△	△
Visual acuity test	△	△	△
Hearing test	△	△	△
PHQ-9	△	△	△

T_0_, pre-intervention (week 0); T_1_, post-intervention (week 12); T_2_,1-month follow-up (week 16); ICOPE, Integrated Care for Older People; MMSE, Mini-Mental State Examination; SPPB, Short Physical Performance Battery; MNA, Mini Nutritional Assessment; PHQ-9, Patient Health Questionnaire-9.

##### ICOPE intrinsic capacity screening tool

2.6.1.1

The assessment of intrinsic capacity strictly follows the five domains proposed by the WHO (33): cognition function, motor function, sensory function (Vision and Hearing), vitality, and psychological function. Each domain is scored as 0 (normal) or 1 (impaired), and the total intrinsic capacity score is the sum of the five domain scores, ranging from 0 to 5. A score of 3 to 5 is defined as low intrinsic capacity, while a score of 0 to 2 is classified as high intrinsic capacity. Specific contents include: ① Cognitive function: Screening assesses memory and temporal orientation, including word recall (flower, door, rice), time and place orientation, and short-term memory tests. An incorrect response or failure to recall all three words indicates a positive screening result. ② Motor ability: The chair rise test is used to assess mobility. Participants must stand up and sit down five times consecutively without using their arms for support, completing the task within 14 s. Failure to meet this requirement is considered a positive screening result. ③ Nutrition: Assesses weight changes and dietary habits over the past 3 months, including whether the individual has experienced weight loss of ≥3 kg or frequently finds food tasteless or difficult to swallow. A “yes” to either question indicates a positive screening result. ④ Vision: Assess whether there are visual difficulties (e.g., watching TV, reading, or recognizing faces) or a history of eye disease treatment. A positive response to either indicates a positive screening result. ⑤ Hearing: Use the whisper test or inquire about subjective hearing perception. Failure in the test or a significant perceived decline in hearing is considered a positive screening result. ⑥ Depression: Assess recent emotional state, including feelings of low mood, depression, or hopelessness, or loss of interest in daily activities. The presence of these symptoms indicates a positive screening result.

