**Methods:**

This mixed-methods study will employ an explanatory sequential design, starting with a quantitative evaluation using a randomized controlled trial (RCT), followed by a supplementary qualitative study. The old patients with disabilities will be randomly allocated in a 1:1 ratio into the intervention group or the control group. The old patients with disabilities in the intervention group will participate in a 12-week “ICOPE-Based Long-Term Care Intervention Program,” and in the control group will maintain their routine life and standard care practices. Participant outcomes in both conditions will be assessed at pre-intervention (T_0_, week 0), post-intervention (T_1_, week 12), and 1 month after the intervention (T_2_, week 16), and a generalized linear mixed model will be used for analysis. The primary outcome is the change in intrinsic capacity, with the significance of the mean difference assessed to determine the intervention effect. In the qualitative part of this study, interviews will be conducted with old patients with disabilities from the intervention group at T_1_ to explore their experiences of receiving the intervention, and content analysis will be applied to the data collected.

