Currently, practice-based projects centered around intrinsic capacity, at the heart of the ICOPE framework, are being gradually launched to improve the quality of care for older adults. These ICOPE practice projects have been implemented in multiple countries worldwide, including France (21) and South Korea (22), achieving significant results. In China, researchers such as Ma et al. (23) conducted a study on 976 middle-aged and older adults (aged 50–97) enrolled in the ICOPE-China project, using the ICOPE screening tool for intrinsic capacity assessments. The study found that 69.1% of participants showed a decline in intrinsic capacity, validating the tool’s effectiveness in identifying declines in the intrinsic capacity of older adults and providing valuable insights for the further development of older adult care in China. Overall, while domestic projects primarily focus on the initial screening of intrinsic capacity, there is still a lack of systematic research and practical application regarding the design and implementation of comprehensive care pathways and intervention programs, particularly for old patients with disabilities in nursing homes.

The main aim of this study is to explore the effects and the experiences of using “long-term care intervention program based on ICOPE for old patients with disabilities in nursing homes” in old patients with disabilities. An explanatory sequential design will be used, starting with a RCT investigating the impact of a long-term care intervention program on intrinsic ability (motor function, cognitive function, psychological function, sensory function, and nutrition) in a group of old patients with disabilities. Subsequently, qualitative surveys will be conducted to gain an in-depth understanding of participants’ subjective experiences of participating in this exergame intervention, in particular the benefits arising from the intervention as well as the influencing factors for participation, which will help understanding the mechanisms behind the therapeutic effects. This information will provide a basis for optimizing, refining, and promoting long-term care intervention program.

We hypothesis that participants in the long-term care intervention program group will experience an improvement of intrinsic ability, compared to those in the control group. Furthermore, we anticipate that these improvements will be maintained at 1-months follow-up.

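### The vitality item looks back 3 months, so at week 16 about two thirds of what it records falls inside the 12-week program, which tends to favour the hypothesis that gains are maintained

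*Protocol article*

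**What the plan says.** Section 2.6.1.1 defines the nutrition (vitality) screen as one that "Assesses weight changes and dietary habits over the past 3 months, including whether the individual has experienced weight loss of ≥3 kg", together with a question on finding food tasteless or hard to swallow. The scoring rule is "A “yes” to either question indicates a positive screening result". For the whole tool, "the total intrinsic capacity score is the sum of the five domain scores, ranging from 0 to 5", so vitality is one point of five.

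The Abstract and Table 2 place T1 at week 12, when the program ends, and T2 at week 16, labelled "1-month follow-up (week 16" in the table footnote. Table 2 applies the ICOPE tool at T0, T1 and T2. No different recall period is given for T2.

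The Introduction states the hypothesis on durability: "Furthermore, we anticipate that these improvements will be maintained at 1-months follow-up". The Abstract says "The primary outcome is the change in intrinsic capacity". Section 2.8 models group by time over all three visits.

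On weight, Table 1 (item 2.3) lists this for the intervention program: "Closely monitor body weight once per week". Section 2.5.3.2 says that controls receive no program component.

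**The concern.** A 3-month look-back suits a single screening visit. Repeated only 4 weeks after the previous visit, it asks mostly about weeks that the previous visit has already covered. If the program improves weight or appetite while it runs, the intervention arm will have fewer positive vitality items at T2 partly because of weeks 3 or 4 to 12, whether or not the benefit outlasts the program. Given such a benefit, the error leans toward the maintenance hypothesis.

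T2 is not just descriptive. It is one of the three time points in the group-by-time model of Section 2.8 and in the repeated-measures power calculation of Section 2.2. On a 0 to 5 scale split between 2 and 3 into high and low capacity, one carried-over point can also decide a resident's class.

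A secondary matter is knowledge of weight. Weekly weighing is listed only in the intervention program, and the Highlights state that participants cannot be blinded. The two arms may therefore answer the weight question from different information. Assessor blinding (Section 2.4) does not remove a difference in self-report. Its direction and size are unknown.

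**Working it through.** The plan gives no figure on this point to reproduce, so the check is arithmetic on its own schedule.

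**Inputs**
- Look-back: 3 months (Section 2.6.1.1). The article does not convert this to weeks, so L = 12 to 13 weeks is assumed.
- Program: weeks 0 to 12. T1 is week 12 and T2 is week 16 (Abstract, Section 2.5.3.1, Table 2).
- Vitality: 1 of 5 points (Section 2.6.1.1).

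**1. Window at T2.** It runs from week 16 − L to week 16. The weeks inside the program number 12 − (16 − L) = L − 4, and the weeks after it number 4.
- L = 12: weeks 4 to 16. Inside 8/12 = 67%, after 4/12 = 33%.
- L = 13: weeks 3 to 16. Inside 9/13 = 69%, after 4/13 = 31%.

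The T1 and T2 windows share the same L − 4 weeks, so they overlap by 67-69%.

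**2. Window at T1.** It runs from week 12 − L to week 12. With L = 12 it is exactly the program. With L = 13 it starts at week −1, and 12/13 = 92% lies in the program. The T1 window therefore matches the period that T1 is meant to assess.

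**3. How much difference could carry over.** This is an illustration, and its weight values are assumptions that are not in the documents: control drift −0.10 kg per week, weekly SD 0.5 kg, intervention-arm drift 0 during the program, L = 13, and loss read as net change over the window. The weight part alone is then positive with probability Φ((−3 − mean)/SD), where SD = 0.5 × √13 = 1.80 kg. At T2:
- Control: mean 13 × (−0.10) = −1.3 kg, Φ(−1.7/1.80), about 17%.
- Intervention, effect fully maintained: mean 0, Φ(−3/1.80), about 5%.
- Intervention, effect gone from week 12: mean 4 × (−0.10) = −0.4 kg, Φ(−2.6/1.80), about 7%.

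The difference between arms is about 12 percentage points with full maintenance and about 10 with none. Under these assumptions most of the T2 difference would remain even if nothing had been maintained. On the 0 to 5 total, 10 points on a 0/1 item is about 0.10.

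**4. Would the 3 kg rule over T1-T2 solve it?** Under the same assumptions the 4-week SD is 0.5 × √4 = 1.0 kg. A loss of 3 kg or more in 4 weeks has probability Φ(−2.6), about 0.5%, in controls and when the effect is gone, and Φ(−3), about 0.1%, when it is maintained. The threshold would almost never be met. The mean T1-T2 change still differs (−0.4 against 0 kg), so the continuous value is the better measure.

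**The case against.** The strongest reply is that the item still responds at T2, that it is one domain of five, and that MMSE, SPPB, MNA, vision, hearing and PHQ-9 are measured at the same visit. All of this stands, and it limits the point to carry-over in one item. MNA does not settle it: the article gives no recall period for it, and it does not enter the 0 to 5 total.

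A second reply is that this is the standard tool and should not be rewritten. That also stands in part. Scoring T2 only from the T1-T2 change would return a resident with a sustained loss to normal and would alter the meaning of the 3 kg threshold. It argues for additions beside the standard item, not for replacing it.

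A reader might infer more than the documents support:
- *That the item cannot register anything after the program.* New loss of 3 kg or more, or new taste or swallowing trouble, in weeks 12 to 16 lies inside the window and scores positive.
- *That a resident who regained lost weight stays positive.* The article does not say whether loss is net or peak to trough. On a net reading the resident is negative.
- *That the T1 result is distorted.* The T1 window is nearly or exactly the program.
- *That controls answer from memory.* The article does not say so. Section 2.5.3.2 includes data collection in controls, and the MNA, which lists weight, is scheduled for both arms.
- *That the primary outcome is compromised as a whole.* The primary outcome is change in intrinsic capacity, and no section names the 0 to 5 total as the primary variable.

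**Conclusion.** The point holds as a limited bias at T2. With 3 months taken as 12 to 13 weeks, 67-69% of the vitality look-back at week 16 falls inside the program and 31-33% after it. The item is diluted by carry-over, and if the program has a vitality benefit, the dilution favours the stated hypothesis of maintenance at 1 month. It affects at most 1 of 5 points. In the illustration about 10 of 12 percentage points would persist without any maintenance, or roughly 0.10 on the total, but that size rests on assumed weight drift and covers the weight question only.

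The T1 contrast is not harmed. Unequal knowledge of weight between unblinded arms is a possible further bias of unknown size. Because the remedy is cheap and the error leans toward a stated hypothesis, the sponsor should make the change.

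**What to change.** - Keep the standard 3-month item at all three visits for the total score.
- Record weight in the same way in both arms at T0, T1 and T2. Section 2.6.1.4 already lists weight in the MNA, but that section lets the MNA stop after six items, so weight should be taken regardless. Use the measured T0-T1 change to answer the weight question at T1.
- At T2, add the appetite and swallowing question with recall since the last visit, and report the measured T1-T2 weight change as a continuous value.
- Base any statement that vitality is maintained on these T2 measures, not on the 3-month item.
- Give a sensitivity analysis of the T2 total score without the vitality item.

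The cost is one extra question at T2, one extra analysis and a weight at each visit, most of which the MNA already provides. A limitation remains: weight loss before T0 can only be recalled, in both arms, so the weight question is recalled at T0 and measured at T1. This applies equally to the two groups and should be stated in the report.
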